### Unintended health consequences of the Swedish parental leave system

Despite the relative generosity of the Swedish parental leave system and its efforts to promote gender equity, some aspects could be responsible for the maintenance or increase in social and health inequities. For example, the strong work-eligibility requirement for earnings based parental leave benefits may exclude groups with less stability in the labour market, such as students and migrants, from benefits equal to those enjoyed by persons with stable incomes.^17^

Inequities in the work-eligibility requirement can emerge in various ways, either by restricting the parental leave benefits scheme to the securely employed and coincidentally excluding parents with ill health (ie, health selection) or by creating health inequities through the unequal distribution of benefits (ie, social causation). For example, individuals with long-term illness may be more likely to have a weak labour market attachment, which in turn can exclude them from earnings related parental leave benefits, thus further increasing socioeconomic inequities. Based on this, we expect that the doubled flat-rate benefits could increase leave uptake among lower-income families or decrease the economic trade-off of using parental leave among lower-income families, thus having potential psychosocial benefits.

Parental leave policies might impact health differently following certain policy reforms. For example, the speed premium supplement introduced to secure earnings based parental leave benefits to parents who have children in quick succession essentially incentivises short birth spacing.^14^ This might lead to increased psychosocial stress and adverse reproductive outcomes among women who become pregnant while simultaneously rearing an infant or toddler. The WHO recommends a minimum of 24 months, assuming 9 months of gestation, before a new conception to avoid adverse reproductive outcomes.^18^ Short birth intervals have been associated with nutrition depletion,^19^ as the mother might not have enough time between births to recover her nutritional reserves and higher risks of weight gain and obesity throughout life.^20^ In turn, these issues are risk factors for adverse outcomes in subsequent children, including low birth weight, preterm birth and perinatal death.^18 21^

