### Aim/objectives and research questions (RQ)

The aim of this project is to evaluate the consequences of parental leave policy in Sweden from a health equity perspective. More specifically, the project will cover the following RQ:

RQ#1: Is eligibility for earnings based parental leave benefits associated with parents’ mental health?

RQ#2: Is short birth spacing in relation to the speed premium supplement reform associated with health problems in the subsequent pregnancy of the mother (early pregnancy obesity) and the subsequent child (low birth weight, preterm and small-for-gestational age)?

RQ#3: Does the introduction and expansion of the father’s quota reserve days influence the mental health of parents after the birth of their child?

RQ#4: Does the introduction of simultaneous parental leave use through the double days reform influence parents’ mental health?

RQ#5: Does the introduction of the father’s quota and double days reforms influence children’s health (episodes of respiratory tract infections, childhood obesity) or health-related outcomes (duration of breast feeding)?

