### Outcomes

Child health outcomes include low birth weight (<2500 g, irrespective of gestational age), preterm birth (<37 gestational weeks) and a small-for-gestational age measure (<10th percentile of birth weight for each gestational age, based on sex-specific Swedish reference curve for normal foetal growth)^41^ from the MBR; hospitalisation episodes of respiratory tract infections during the first 2 years of life (International Classification of Diseases-10 (ICD-10) Codes J20.5, J21.0, J21.9, J20.9, J18.9, J12.9 and J22.9) from the NPR and duration of partial or exclusive breast feeding (at months 2, 4, 6, 9 and 12) as well as childhood obesity (body mass index (BMI); weight in kilograms/height in meters^2^ using age-specific and sex-specific cut-offs for children’s overweight and obesity^42 43^ at 18 months and 3–5 years) from the CHR. Maternal health outcomes include maternal early pregnancy overweight (BMI 25–29.9 kg/m^2^) and obesity (BMI 30–39.9 kg/m^2^).^44^

Mental health outcomes will be assessed for both parents using count data on purchases of prescription anxiolytic and antidepressant medications (Anatomical Therapeutic Classification Codes N05B and N06A, respectively) as well as outpatient visits and hospitalisations with a primary diagnosis of mental and behavioural disorders (until 1997, ICD-9 Codes 290–319; thereafter, ICD-10 Codes F00-F99), from childbirth to 18 and 36 months after birth.

Outcomes will be expressed as prevalence or rates, given availability of follow-up time.

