### Covariates

Annual information on parental leave uptake (number of days) for each parent will also be available from LISA. Specific information on parental leave eligibility and uptake (including length of paid and unpaid leave) will be retrieved from the SIAD.

Demographic characteristics will include parents’ age at childbirth, country of birth (ie, Swedish vs other and specific origins) and marital and cohabitation status, from the TPR and LISA. Sociodemographic characteristics including educational attainment, household disposable income, individual labour income, employment status and receipt of sick leave benefits will be drawn from LISA.

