### Study design and statistical analyses

A variety of advanced designs and statistical methods for observational data will be applied. First, using descriptive and correlational designs, we will implement standard multivariable methods to quantify links between prebirth health conditions, parental leave eligibility and uptake, and postbirth health outcomes while accounting for confounding using relevant covariates and heterogeneity analyses.

Second, we will use robust quasi-experimental approaches to assess the causal effects of parental leave policy on health, reducing the risk of selection effects and unmeasured confounding by harnessing the natural, ‘as-if’ randomisation around policies.^45 46^ With this approach, we can isolate the absolute policy effects on health even in the absence of detailed information on changes in parental leave uptake. These approaches include interrupted time series (ITS), regression discontinuity (RD) and difference-in-difference (DiD) designs. For ITS designs, segmented regression models will be adjusted for seasonality and trend while accounting for autocorrelation.^46^ For RD designs, continuity around the cut-off will be tested using the McCrary Density Test and similarity of eligible and ineligible observations will be determined through descriptive statistics. Finally, for DiD designs, we will examine the data to confirm parallel trends and other relevant assumptions.^45^

RQ#1: We will examine the effects of the 2002 doubling of flat-rate benefits on the mental health of parents. An RD design will be applied to plot psychiatric hospitalisation rates with labour income as a forcing variable, with separate plots before (with an income cut-off equivalent to 75 SEK, at 80% reimbursement rate) and after 2002 (with a cut-off equivalent to 150 SEK daily). Cut-offs for both parents’ income will be examined. We will triangulate our findings with a DiD approach, comparing those eligible for the increased benefits to those ineligible before and after reforms.

RQ#2: A segmented-regression ITS of monthly birth data comparing the rate of low birth weight and preterm births 3 years before and after the 1980 and 1986 speed premium reforms will be implemented. We will also compare the prevalence of obesity in mothers early in their second pregnancy before and after the reform.

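### RQ#2 compares obesity prevalence at the second pregnancy without using first-pregnancy BMI, which costs precision and leaves the comparison open to a shift in prior obesity

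*Protocol article*

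**What the plan says.** The research question (Protocol article, Aim/objectives and research questions) asks whether short spacing in relation to the speed premium is "associated with health problems in the subsequent pregnancy of the mother (early pregnancy obesity") and with three outcomes in the subsequent child. The analysis text for RQ#2 (Study design and statistical analyses) specifies a segmented-regression interrupted time series of monthly births for low birth weight and preterm birth. It then adds: "We will also compare the prevalence of obesity in mothers early in their second pregnancy before and after the reform".

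The Outcomes section defines the measure by BMI class at one time point. It begins "Maternal health outcomes include maternal early pregnancy overweight" (BMI 25-29.9) and goes on to obesity (BMI 30-39.9). It also states: "Outcomes will be expressed as prevalence or rates, given availability of follow-up time".

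The reason for studying maternal weight is in the section on unintended health consequences, where short intervals are linked to "higher risks of weight gain and obesity throughout life".

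The Covariates section lists "Demographic characteristics will include parents’ age at childbirth, country of birth" and marital and cohabitation status, then "Sociodemographic characteristics including educational attainment, household disposable income, individual labour income, employment status and receipt of sick leave benefits". Maternal BMI and weight are not listed.

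**The concern.** The proposed mechanism acts in the interval between the first and second pregnancy. Obesity already present early in the first pregnancy cannot result from that interval, yet it enters the outcome in full. Three things follow.

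- **Precision.** Cases the reform could not have caused add variance to both periods.
- **Scale.** On a ratio scale they pull any true effect towards 1.
- **Bias.** If the proportion of second-time mothers who were already obese differs between periods, prevalence moves even when spacing has no effect on weight.

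The Limitations section accepts that the speed premium may have altered who had children. Its planned check compares sociodemographic characteristics before and after each reform, which would not directly show a shift in prior BMI.

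**Working it through.** **Is first-pregnancy BMI used anywhere?** The places that could supply it do not:

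- Covariates: no BMI or weight.
- Study design: prebirth health conditions are mentioned for the general correlational step, without naming BMI or RQ#2.
- Additional analyses: the maternal-weight sensitivity analysis concerns missing data. The example given of a falsification outcome is prebirth hospitalisation.
- Limitations: the composition check covers sociodemographic characteristics.

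**Size.** The article states no prevalence, incidence, sample size or power for this outcome, so there is no figure to reproduce. All inputs here are assumptions.

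Let p = obesity at the first pregnancy, s = share of those women still obese at the second, and i = new obesity by the second pregnancy among women not obese at the first.

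- Prevalence at the second pregnancy: P = p·s + (1 − p)·i
- Share already obese at the first: p·s / P
- True effect: replace i by 1.2·i
- Shift in prior obesity only: replace p by 1.1·p

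Worked example with p = 0.08, s = 0.85, i = 0.02:

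- P = 0.068 + 0.92 × 0.02 = 0.0864. Share already obese = 0.068 / 0.0864 = 79%.
- True effect: P = 0.068 + 0.92 × 0.024 = 0.09008. Ratio 1.043.
- Shift only: P = 0.088 × 0.85 + 0.912 × 0.02 = 0.09304. Ratio 1.077.

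| p, s, i | P | Already obese | Ratio, true +20% in new obesity | Ratio, +10% in p only | Absolute difference, true effect: prevalence vs new obesity (points) |
|---|---|---|---|---|---|
| 0.03, 0.75, 0.04 | 0.0613 | 37% | 1.127 | 1.035 | 0.78 vs 0.80 |
| 0.05, 0.75, 0.03 | 0.0660 | 57% | 1.086 | 1.055 | 0.57 vs 0.60 |
| 0.05, 0.85, 0.03 | 0.0710 | 60% | 1.080 | 1.058 | 0.57 vs 0.60 |
| 0.08, 0.85, 0.02 | 0.0864 | 79% | 1.043 | 1.077 | 0.37 vs 0.40 |
| 0.08, 0.85, 0.04 | 0.1048 | 65% | 1.070 | 1.062 | 0.74 vs 0.80 |

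In this model the new-obesity measure would show a ratio of 1.20 for the true effect and 1.00 for the shift in p alone.

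**Absolute scale.** The prevalence difference equals (1 − p) times the difference in new obesity, so 92-97% of it is kept.

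**Precision.** From the squared ratio of two-sample z-scores, the new-obesity measure needs 1.5-4.4 times fewer women at risk. After counting the obese women it excludes, the gain is 1.5-4.1 times.

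**A second set of assumptions** (p = 2-8%, i = 1-3%, s = 80%) gives 35-87% already obese and a ratio of 1.03-1.13 for the same true effect. At p = 5% and i = 2%, with 80% power and two-sided 5%, about 21,109 women at risk per period are needed for new obesity (2.0% vs 2.4%). Prevalence needs about 62,172 women per period (5.90% vs 6.28%).

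**The case against.** The strongest defence is that status at the second pregnancy is what RQ#2 asks about. Obesity at that time is relevant to the subsequent child whenever it began, so prevalence is a legitimate estimand and new obesity is a different one. This stands, and it is why prevalence should be kept.

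A reader might infer that women already obese are counted as events of short spacing. The article does not support that. It compares two periods and attributes no woman's obesity to her interval, and such women appear on both sides. A reader might also infer that most of the effect is lost. That is true only of a ratio. The article speaks of absolute policy effects and fixes no ratio measure for this outcome, and the absolute difference is largely kept. Nor does the BMI 30 cut-off ignore large gains below it: a woman going from BMI 21 to 28 falls in the overweight class, which is a listed maternal outcome.

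Composition is partly addressed through subgroup analyses, before/after comparison of population characteristics, and optional falsification dates and outcomes. None of these names BMI. The article's own selection concern is eligibility for earnings based benefits, so the 10% shift in prior obesity is an assumption. The added analyses are no complete cure either, since selection can also change the risk of new obesity. Trend adjustment, if the segmented model is meant to cover obesity as well, could absorb a smooth rise in BMI but not a step in composition at the reform.

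The most practical objection is missing data. The article says weight is less well recorded in women who appear to be of normal weight, and a recorded non-obese first BMI draws on exactly that group. In the first scenario the precision gain disappears if fewer than about 67% of at-risk women have a usable first record (1 / (1.54 × 0.97)). Completeness around 1980 and 1986 is not stated. This rules out simply replacing the outcome.

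**Conclusion.** The point holds as a worthwhile improvement to a stated analysis; the planned outcome is not invalid. The maternal comparison leaves out the one pre-exposure measure most directly tied to its mechanism, and the planned composition checks could miss a shift in it. On the assumed inputs, the ratio from a modest shift in prior obesity (1.035-1.077) overlaps the ratio from a true 20% rise in new obesity (1.04-1.13). In one of the five scenarios it exceeds it. Prevalence alone therefore cannot reliably separate the two. The loss on the absolute scale is small; the precision loss may be substantial but depends on how complete the first-pregnancy records are. Every magnitude rests on assumed rates. That first-pregnancy BMI goes unused rests on the text alone.

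**What to change.** Keep the before/after comparison of second-pregnancy prevalence and add to RQ#2:

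1. the same comparison adjusted for early first-pregnancy BMI;
2. new obesity at the second pregnancy among women with a recorded non-obese first-pregnancy BMI, with BMI change between the two pregnancies as support;
3. a comparison of first-pregnancy BMI before and after each reform, as a composition check.

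Apply the same maximum birth interval in every month, so that availability of the first record does not vary along the series.

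The cost is a few sentences and a within-woman link in the medical birth register, which the article already links from 1973. The real downside is the need for two weight records per woman. Report completeness of both by period, and extend the planned missing-weight sensitivity analysis to the first-pregnancy record. Where completeness around a reform is too low, label the added analyses as supportive only.

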### Additional analyses

Given the potential for effect modification and compositional changes in the study populations, subgroup analyses by parents’ sociodemographic characteristics (ie, annual labour income, to determine eligibility for earnings based benefits or educational attainment) will be considered for all RQ. Analyses by parents’ nativity will be implemented for RQ#2–4, given differential responses to the policies by Swedish-born and foreign-born parents.^14^ Other relevant parental characteristics, that is, age at childbirth and cohabitation status, will also be considered.

Sensitivity analyses will be performed to account for systematically missing data, such as maternal weight (ie, given that women appearing to be of normal weight are less monitored for obesity).^47^ For studies examining first births, sensitivity analyses restricting mental health outcomes to the 18 months post birth will be considered in order to exclude the potential health effects related to a second pregnancy.

For all ITS designs, we will specify multiple intervention points to assess the possibility of lagged policy effects. Robustness analyses of falsification (‘pseudo-intervention’) dates and falsification outcomes (eg, prebirth hospitalisations) will also be considered.

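### RQ#2 specifies maternal early-pregnancy obesity only as a before/after prevalence comparison, which cannot separate calendar drift from the speed premium

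*Protocol article*

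**What the plan says.** The Aim/objectives and research questions section of the protocol article makes maternal obesity a named outcome of RQ#2. The question concerns "health problems in the subsequent pregnancy of the mother", with early pregnancy obesity given in brackets, alongside outcomes of the subsequent child.

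Under Study design and statistical analyses, RQ#2 has two sentences. The first covers the child. It gives low birth weight and preterm birth a monthly segmented regression and fixes the window and both reform years: "3 years before and after the 1980 and 1986 speed premium reforms will be implemented". The second covers the mother, and says: "We will also compare the prevalence of obesity in mothers early in their second pregnancy before and after the reform".

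The same section promises trend adjustment for one class of design: "For ITS designs, segmented regression models will be adjusted for seasonality and trend while accounting for autocorrelation". Additional analyses ties lag points to that class as well: "For all ITS designs, we will specify multiple intervention points to assess the possibility of lagged policy effects".

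**The concern.** Two outcomes of one research question receive different methods in adjacent sentences. The child outcomes get a design that models the pre-reform trend. The maternal outcome gets a comparison of two prevalences.

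If recorded early-pregnancy obesity was moving over calendar time for any reason, the two periods would differ even if the speed premium did nothing. The article itself points to one possible route. Additional analyses notes that women who look to be of normal weight are monitored less for obesity, so a change in recording over the years could shift recorded prevalence.

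The introduction links short intervals to weight gain and obesity, so an upward drift would look like the expected harm. A downward drift would hide a real one.

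**Working it through.** **1. What the text fixes, side by side.**

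| Item | Low birth weight, preterm birth | Maternal obesity |
|---|---|---|
| Design | Segmented-regression ITS, monthly | Prevalence before and after |
| Reform | 1980 and 1986 | Singular, year not given |
| Window | 3 years each side | Not given |
| Trend, seasonality, autocorrelation | Yes, as an ITS | Not stated |
| Comparison series | Not stated | Not stated |

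RQ#5 explicitly places the prevalence of childhood obesity inside an ITS. The article therefore names the design for an obesity prevalence elsewhere, but does not do so here.

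**2. Expected value of the contrast.** Let drift be linear at *s* points a year, with adjacent windows of *w* years each side. The window centres are *w* years apart, so

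expected difference = reform effect + *s* × *w*.

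The plan has no figure to reproduce: it states no prevalence, drift, number of second pregnancies or obesity window. The rest is illustration. I assume *w* = 3, borrowed from the ITS sentence, and no reform effect. The spurious difference is then 3 × 0.05 = 0.15 points at the low end and 3 × 0.3 = 0.9 points at the high end.

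**3. Chance of a significant result from drift alone.** With *n* women per period, prevalences p1 and p2 and difference d,

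SE = √[p1(1−p1)/n + p2(1−p2)/n], and chance = Φ(d/SE − 1.96).

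This counts only results in the direction of the drift, at two-sided 0.05. Example: 5.0% against 5.3% with n = 60,000 gives SE = 0.128 points, d/SE = 2.35 and Φ(0.39) = 65%. At an assumed 5% baseline:

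| Drift (points/year) | Spurious difference (points) | n = 5,000 | n = 20,000 | n = 60,000 |
|---|---|---|---|---|
| 0.05 | 0.15 | 5% | 10% | 22% |
| 0.1 | 0.30 | 10% | 27% | 65% |
| 0.2 | 0.60 | 27% | 76% | above 99% |
| 0.3 | 0.90 | 51% | 98% | above 99% |

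**4. Would the plan's own model cure it?** I simulated 72 monthly prevalences, 36 on each side, in 1,000 runs per setting. Assumptions: 1,500 second pregnancies a month (54,000 per period), 5% prevalence at the reform date, linear drift and no reform effect. Each series was fitted with a before/after model and with a segmented model (pre-slope, level change, slope change).

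| Drift (points/year) | Before/after: mean difference | Before/after: false positives | Segmented: mean level change | Segmented: false positives |
|---|---|---|---|---|
| 0 | 0.00 | 4.8% | −0.01 | 4.4% |
| 0.1 | 0.30 | 58% | 0.00 | 4.3% |
| 0.2 | 0.60 | 99% | 0.01 | 3.9% |
| 0.3 | 0.89 | 100% | −0.01 | 4.0% |

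The simulation had no seasonality or autocorrelation, and the drift was exactly linear. It shows the mechanism and does not predict the result of the study.

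**The case against.** The strongest reply is that this is a condensed article and the sentence names no model, so silence is being read as a commitment. Before-and-after wording is also how the article describes its ITS analyses: RQ#3, RQ#4 and RQ#5 all speak of births before and after a reform. The obesity sentence directly follows an ITS sentence and opens with 'also'. The abstract says that health outcomes will be compared by ITS, difference-in-difference and regression discontinuity. On that reading obesity is already inside the segmented regression.

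This has some force. A reader might infer that the plan commits to an unadjusted test, but the text does not say so. It does set out designs outcome by outcome, names ITS for the RQ#5 obesity prevalence, and names it in RQ#2 only for the other two outcomes. The specific sentence is what an analyst would follow.

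A reader might also infer that this is the only planned analysis touching maternal obesity. The documents do not support that. Study design and statistical analyses opens with multivariable methods, and Additional analyses plans nativity splits for RQ#2–4 and considers income subgroups for all questions. Limitations promises checks of population composition around each reform. None of these models a calendar trend in the outcome. Falsification dates could expose drift, but they are only to be considered, in a paragraph that begins with ITS designs. The maternal-weight sensitivity analysis addresses missing data.

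Finally, a reader might infer that national numbers guarantee a highly significant result from drift alone. With 105,000 women per period (assumed) and drifts of 0.1, 0.2 and 0.3 points a year from 4%, 5% and 6%, z is 3.4, 6.1 and 8.4. Those values follow only from those inputs. The article gives neither the direction of any trend nor the number of women with a recorded weight, which it treats as systematically missing.

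**Conclusion.** The point holds as a defect in the stated analysis of a named outcome. As written, the maternal obesity contrast equals the reform effect plus drift per year times the distance between window centres, and no other provision clearly removes the second term.

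The mechanism follows from the design. The size does not: it rests on an assumed baseline, linear drift, number of women and 3-year window. The documents also do not show that obesity was rising, so the direction of any bias is open. The unnamed reform year and window add to the problem, because the drift term depends on both.

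**What to change.** Analyse early-pregnancy obesity in second pregnancies with the monthly segmented regression already specified for RQ#2: pre-reform trend, level change, slope change, seasonality and autocorrelation. Name both the 1980 and the 1986 reform and apply the stated window of 3 years each side. Keep the raw before/after prevalence as a descriptive figure without a test. Apply the planned missing-weight sensitivity analysis to the same monthly series.

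A control series would strengthen this but is optional. Candidates are first pregnancies in the same months, or mothers not eligible for earnings based benefits. Indexing by month of conception is likewise a choice for the authors.

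The cost is one further model run and less precision. With m = 36 equally spaced months per side, the variance of a fitted line at the break is σ²/m × [1 + 18²/((36² − 1)/12)] = σ²/m × (1 + 3.0), against σ²/m for a simple mean. The standard error of the level change is therefore about twice that of the raw difference, before seasonality and autocorrelation are added.

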RQ#3: We will conduct an ITS analysis of parents of children born before and after the 1995 father’s quota reform using segmented regression to capture changes in psychiatric hospitalisation rates up to 36 months after childbirth, based on fathers’ eligibility for the father’s quota.

RQ#4: An ITS for parents to children born before and after the 2012 double days reform will be implemented to capture changes in the number of outpatient visits for mental health and psychotropic prescriptions within 36 months after childbirth, by child’s month of birth.

RQ#5: We will implement separate ITS analyses of children born before and after the 1995 father’s quota and 2012 double days reforms, comparing hospitalisation rates for diagnoses of respiratory tract infections (in children under 2), prevalence of childhood obesity (at 18 months and 3–5 years) and changes in breastfeeding duration.

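### Maternal overweight is a listed outcome with no named analysis in RQ#2, it is unclear whether an overweight child counts as an event in RQ#5, and the maternal weight outcomes are closed bands

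*Protocol article*

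**What the plan says.** **Mothers.** The Outcomes section of the protocol article gives two weight outcomes: "Maternal health outcomes include maternal early pregnancy overweight (BMI 25–29.9 kg/m^2^) and obesity (BMI 30–39.9 kg/m^2". The research question is narrower. RQ#2, under Aim/objectives and research questions, asks about "health problems in the subsequent pregnancy of the mother (early pregnancy obesity". The RQ#2 paragraph under Study design and statistical analyses will "compare the prevalence of obesity in mothers early in their second pregnancy before and after the reform". Overweight appears in neither RQ#2 text.

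**Children.** Outcomes has one weight outcome, labelled childhood obesity. It is based on BMI, "using age-specific and sex-specific cut-offs for children’s overweight and obesity". The RQ#5 paragraph reuses the label: it will compare "prevalence of childhood obesity (at 18 months and 3–5 years) and changes in breastfeeding duration".

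**Context.** The introduction links short birth intervals to weight gain as well as to obesity. The Data section says child weight data come from two counties. Additional analyses notes that maternal weight is systematically missing, because women who appear to be of normal weight are monitored less for obesity.

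**The concern.** There are three linked problems.

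1. **A listed outcome has no named analysis.** Maternal overweight is defined but assigned to no comparison. The stated mechanism includes weight gain, which can take a woman from normal weight into overweight without making her obese.
2. **The child event is not fixed.** The prevalence of childhood obesity has two readings, with different numerators, depending on whether an overweight child is counted. Left open, the choice could be made after the data are seen.
3. **The maternal categories are closed.** A woman who moves from BMI 29 to 31 leaves the overweight band, so part of a worsening cancels within that outcome. The obesity band has the same defect at its upper end: as written, a woman with BMI 40 or more is in neither category.

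At stake is whether a general upward shift in weight would be seen, and whether the reported weight results can be traced to one pre-stated definition.

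**Working it through.** **Step 1. The texts side by side**

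| | Outcomes | Research question | Analysis paragraph |
|---|---|---|---|
| Mothers (RQ#2) | overweight 25–29.9; obesity 30–39.9 | obesity | obesity |
| Children (RQ#5) | childhood obesity, with overweight and obesity cut-offs | childhood obesity | childhood obesity |

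For mothers the analysis is narrower than the outcome list. For children the label is the same throughout, but its content is ambiguous.

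**Step 2. No figure to reproduce.** The article gives no weight prevalence, number of births, effect size or power. All inputs in Steps 3 to 5 are assumptions, used only to show the range.

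**Step 3. General shift, log-normal BMI.** Assume the median BMI rises by 1%. For a category with prevalence P, the standardised change is d = ΔP / √(P(1−P)). For mean log BMI it is ln(1.01) / (log SD). The required sample size is proportional to 1/d², so the sample-size ratio of two outcomes is the squared ratio of their d values. Ratios are from unrounded values.

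| Median, log SD | BMI ≥30 | BMI ≥25 | Band 25–29.9 | d: ≥30 / ≥25 / band / mean |
|---|---|---|---|---|
| 22, 0.13 | 0.85→1.05% | 16.3→18.2% | 15.4→17.2% | 0.021 / 0.053 / 0.049 / 0.077 |
| 22.5, 0.13 | 1.35→1.63% | 20.9→23.2% | 19.5→21.5% | 0.025 / 0.056 / 0.050 / 0.077 |
| 23, 0.15 | 3.83→4.41% | 28.9→31.2% | 25.1→26.8% | 0.031 / 0.051 / 0.040 / 0.066 |

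- Sample size for BMI ≥30 relative to BMI ≥25: 6.3, 5.0 and 2.8.
- With the protocol's own obesity band (30–39.9) in place of ≥30, the ratios are almost the same: 6.3, 5.0 and 2.8.
- Sample size for the closed band 25–29.9 relative to BMI ≥25: 1.18, 1.25 and 1.64.
- In the third row, prevalence at BMI ≥25 rises by 2.3 points but the band rises by only 1.7. The missing 0.6 points are women who crossed 30.

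**Step 4. General shift, normal BMI, other prevalences.** The information kept by a cut-off with tail prevalence p is φ(z)² / [p(1−p)], where z is the normal quantile of the cut-off. Sample sizes are per period, for 80% power at two-sided 5% and a shift of 0.03 SD.

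| Obese / overweight-or-obese | Information ratio | N, obesity | N, overweight-or-obese | Ratio |
|---|---|---|---|---|
| 2% / 12% | 0.32 | 142,136 | 45,415 | 3.1 |
| 3% / 18% | 0.34 | 107,130 | 37,011 | 2.9 |
| 5% / 22% | 0.44 | 76,368 | 33,851 | 2.3 |
| 12% / 38% | 0.62 | 45,415 | 28,254 | 1.6 |

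Taken with Step 3, the range is about 1.6 to 6 times.

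In terms of power, at 3%/18% with 90,000 per period:

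- A 0.02 SD shift gives 40% for obesity against 83% for overweight-or-obese.
- A 0.03 SD shift gives 73% against 99%.
- A 0.05 SD shift gives 99% against 100%.

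With 10,000 per period and 0.05 SD it is 30% against 68%. Over 3,000 to 90,000 per period and 0.01 to 0.05 SD, the relative loss of power runs from nil to about 60%.

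**Step 5. Only the obese tail rises.** Let obesity rise by 10% relative, from 3.0% to 3.3%, and overweight-or-obese by the same 0.3 points, from 18.0% to 18.3%. With 90,000 per period, obesity alone has 95% power and overweight-or-obese 38%. The ranking reverses.

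Steps 4 and 5 treat the comparison as a simple before/after contrast. They ignore the time-series structure, autocorrelation and missing weights, so the absolute powers are optimistic. The child outcome was not computed.

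**The case against.** The strongest case against the point is that obesity is a legitimate, pre-stated endpoint: the RQ#2 question and its analysis agree with each other. The article is condensed, and its analysis paragraphs are visibly abbreviated. Small-for-gestational age is in the RQ#2 question and is defined under Outcomes, yet the RQ#2 analysis paragraph omits it too. An outcome left out of a one-sentence summary may still be analysed. The maternal data are total-population registers, where the loss is small unless the shift is very small. The speed premium acts through women who shorten birth spacing, so a uniform shift in all mothers is doubtful.

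Much of this stands. It rules out the stronger reading, which a reader might infer, that counting obesity only wastes most of the power. That needs prevalences, numbers and effect sizes that the documents do not give, and Step 5 shows the ranking can reverse. A reader might also infer that RQ#5 excludes overweight children. The text does not show this, because the childhood obesity label itself carries overweight cut-offs. Nor do the two-county child data, whose size is not given, establish that RQ#5 would end in an uninformative null.

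The objection does not remove the mismatch between the maternal outcome list and RQ#2, the undefined child event, or the closed bands. The reversal in Step 5 is a reason to report both obesity and overweight-or-obese.

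One further objection is sound. Weights are missing selectively among women who appear to be of normal weight. If that missingness changes over time, it may disturb BMI ≥25 and mean BMI more than it disturbs obesity.

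**Conclusion.** The point holds as a mismatch and a weak choice of categories. Maternal overweight is listed but not named in RQ#2, the event in RQ#5 is ambiguous, and both maternal categories are closed bands. This part rests on the text alone.

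The size of the precision loss is conditional. If BMI shifts generally, obesity alone needs about 1.6 to 6 times the sample of overweight-or-obese under the assumed distributions, and the closed 25–29.9 band needs about 1.2 to 1.6 times. If only the obese tail rises, obesity loses nothing and can be the stronger outcome. The documents do not say which case applies. The planned secondary outcomes should therefore cover both, with obesity still leading.

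**What to change.** - **Keep obesity as the main weight outcome** in RQ#2 and RQ#5. Define maternal obesity as an open category, BMI 30 or more.
- **Replace the stand-alone 25–29.9 band** with two secondary outcomes: overweight-or-obese (maternal BMI 25 or more; child at or above the overweight cut-off) and mean BMI, age- and sex-standardised in children.
- **State under Outcomes which category is the event**, for mothers and for children. Use the same terms in the research questions and in the RQ#2 and RQ#5 analysis paragraphs.
- **Extend the planned sensitivity analysis for missing maternal weight** to the added maternal outcomes.

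The cost is a few extra models on variables the project already plans to use, and one or two more secondary outcomes to report. The drawback is that these outcomes may be more sensitive than obesity to selectively missing weights, so the sensitivity analysis should be reported beside them.
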